## Abstract

**Background:**

The trial aims to evaluate whether neonatal mortality can be reduced through systemic changes to the provision and promotion of healthcare. Neonatal mortality rates in India are high compared to other low income countries, and there is a wide variation of rates across regions. There is evidence that relatively inexpensive interventions may be able to prevent up to 75% of these deaths. One area with a particularly high rate is Mahabubnagar District in Andhra Pradesh, where neonatal mortality is estimated to be in the region of 4–9%. The area suffers from a vicious cycle of both poor supply of and small demand for health care services. The trial will assess whether a package of interventions to facilitate systemic changes to the provision and promotion of healthcare may be able to substantially reduce neonatal mortality in this area and be cost-effective. If successful, the trial is designed so that it should be possible to substantially scale up the project in regions with similarly high neonatal mortality throughout Andhra Pradesh and elsewhere.

**Methods/Design:**

This trial will be a cluster-randomised controlled trial involving 464 villages in Mahabubnagar District. The package of interventions will first be introduced in half of the villages with the others serving as controls. The trial will run for a period of three years. The intervention in the trial has two key elements: a community health promotion campaign and a system to contract out healthcare to non-public institutions. The health promotion campaign will include a health education campaign, participatory discussion groups, training of village health workers and midwives, and improved coordination of antenatal services. The intervention group will also have subsidised access to pregnancy-related healthcare services at non-public lth centres (NPHCs).

The primary outcome of the trial will be neonatal mortality. Secondary outcomes will include age at and cause of neonatal death, neonatal morbidity, maternal mortality and morbidity, health service usage, costs and several process and knowledge outcomes.

**Discussion:**

The trial will be run by independent research and service delivery arms and supervised by a trial steering committee. A data monitoring committee will be put in place to monitor the trial and recommend stopping/continuation according to a Peto-Haybittle rule. The primary publication for the trial will follow CONSORT guidelines for cluster randomised controlled trials. Criteria for authorship of all papers, presentations and reports resulting from the study will conform to ICMJE standards.

**Trial Registration:**

Current Controlled Trials ISRCTN24104646

## Background

### Research justification and relevant literature

Neonatal mortality accounts for almost 40% of all deaths of children under five worldwide, approximately 3.9 million deaths annually [1]. (neonatal mortality and other terms of interest are defined in Table 1 in the appendix) The *Lancet Neonatal Survival Series *asserts that a very small group of causes – including severe infection, prematurity, and birth asphyxia/childbirth complications – lead to the vast majority of these deaths [2]. These and the other major causes of neonatal mortality result in three million newborn deaths that "could be prevented annually by improving access to the low-cost, low-tech interventions that are not currently reaching those most in need," [3]. Our trial tests whether a functional, cost-effective and scalable programme, based on interventions suggested by this literature, can reduce neonatal mortality.

**Table 1 T1:** Glossary of terms

Neonatal Mortality Rate	Number of deaths during the first 28 completed days of life per 1000 live births in a given year.
Perinatal Mortality Rate	The number of perinatal deaths per 1000 total births in a given year. The perinatal period starts at the beginning of foetal viability (28 weeks gestation) and ends at the end of the 7th day after delivery. Perinatal deaths are the sum of stillbirths plus early neonatal deaths.
Infant Mortality Rate	Number of children dying under a year of age per 1000 live births in a given year.
Village Health Worker	A local woman from the village trained primarily to deliver health education to eligible women and refer them to the midwife for antenatal pregnancy-related and postnatal services.
Gram Panchayat	The Gram Panchayat is the executive organ of the Gram Sabha, an agency for planning and development at the village level. Its size varies from 15–30, and the population it covers also varies widely from 5,000 – 15,000. The members of the Panchayat hold office for 3–4 years. Every Panchayat has an elected President (Sarpanch) and the Vice president (Panchayat Secretary) The powers and functions of the Panchayat Secretary are very wide – they cover the entire field of civic administration, including sanitation and public health and of social and economic development in the villages.
Thanda	Administratively, a thanda refers to a hamlet with a small population (around 100 households) vis-à-vis 'villages'. Each thanda is considered a part of a nearby village although the two habitations could be distant from each other.
Penta	A Tribal Chenchu village is known as a "penta". Each penta consists of few huts that are spaced apart and are grouped together based on kinship pattern. The close relatives live nearby and the distant ones farther away. Their homes comprise of few belongings and are generally sparse and Spartan in appearance.
Anganwadi Worker	Angan literally means "courtyard." Under the Integrated Child Development Services Scheme, there is an Anganwadi worker for each population of 1000 people. She is selected from the community and undergoes training in various aspects of health, nutrition and child development. She is a part time worker and is paid an honorarium for service including health checkups, immunisation, supplementary nutrition, health education, and informal preschool education and referral services for women in general and children below the age of 6 years.
DALYs	Disability Adjusted Life Years is the sum of years of potential life lost due to premature mortality and the years of productive life lost due to disability.
Gram Sabha	An assembly of all the adults of a given village which meets at least twice in a year. The Gram Sabha considers proposals for taxation, discusses annual programmes and elects members of the Gram Panchayat.

The methods for implementing this programme are also derived from the public health literature. There is a growing body of evidence showing the potential efficacy of community interventions to address public health problems and disseminate health knowledge, however there exists a large research gap in the literature evaluating such interventions [4-7,3]. Similarly, contracting out of health service provision to non-public enterprises appears promising, yet is also under-researched [8-11]. Our study looks to investigate the potential of these two types of intervention in tandem and in the context of the Lancet Neonatal Survival Series findings [2].

The multi-faceted approach the trial adopts is also rooted in the literature on public health interventions. McLeroy et al. emphasize the need for public health interventions to approach health problems on social and environmental levels, as well as at the individual level, in order to obtain significant results [12]. Others have suggested that multi-faceted health interventions have greater likelihood of success than those which target individuals alone [13,14].

Aside from the obvious motivation of rapidly and significantly reducing neonatal mortality, these interventions also have great promise in their sustainability and knock-on effects. Investments in maternal education are largely recognized to have long-term positive effects on child survival [15]. Similarly, there is evidence that infant morbidity due to infection is significantly related to lifelong disease-related impairment [16,17]. Improvement in maternal education and reduction of infant morbidity as a result of our intervention may yield long-term benefits beyond the time-scale of the trial.

### Background information on the trial area

Neonatal mortality constitutes 65% of all infant deaths in India [18]. In the last three decades, consistent efforts have been underway to reduce child mortality by emphasizing universal immunization, oral rehydration therapy and control of respiratory tract infections. While infant mortality in India has declined from 129 (per 1000 live births) in 1970 to about 68 in 2000, the fate of neonates has remained virtually unaltered: one out of 22 infants in India does not reach the second month of life [19,20].

The state of Andhra Pradesh reports an aggregate neonatal mortality rate (NMR) of 44 per 1000 live births [20]. There is very little reliable information quantifying neonatal survival rates in rural areas and tribal regions, although these rates are known anecdotally to be even higher.

In 1998, a survey in the Mahabubnagar district of Andhra Pradesh found infant mortality rates (IMR) to be much higher than the national average. Summarised results of this survey are shown in Table 2.

**Table 2 T2:** District and division-level estimates of Infant Mortality Rate with 95% confidence levels in Mahabubnagar district of Andhra Pradesh [20]

**Area**	**IMR***	**95% CI**
Mahabubnagar district (overall)	*115*	*107 *– *122*
Gadwal division	93	60 – 127
Mahabubnagar division	110	91 – 128
Narayanpet division	125	102 – 147
Wanarparthy division	62	35 – 89
Nagarkurnool division	140	117 – 163

*Infant mortality rate per 1000 live births

The Nagarkurnool division of Mahabubnagar had an infant mortality rate of 140 per 1000 live births. It is believed that approximately 50% of the infant deaths in this division occur in the first month of life [20]. We have chosen to conduct the trial in the Nagarkurnool division in Mahabubnagar on account of the high mortality rate in the area.

Any strategy to reduce neonatal mortality faces several important obstacles. First, a substantial fraction of births occur in unsafe conditions, usually at home. This reflects longstanding traditions and lack of knowledge regarding safe birth practices. Second, institutional care at public health facilities is often geographically inaccessible. Third, even if distance is not a problem, these facilities also suffer chronically from lack of medical practitioners and insufficient medical supplies. The problem faced is thus threefold: health knowledge, demand for health care, and supply of good quality health care are all insufficient. The trial intervention will augment all of these components in order to assess whether, together, they substantially reduce neonatal mortality rates.

### Objectives

The aim of the trial is to test the hypothesis that a community health promotion campaign, in combination with improved supply of health services through contracting out to the non-public sector, can lead to a substantial reduction in neonatal mortality. The programme is designed to improve health knowledge while enhancing both demand for, and supply of, health care.

An important element of the trial is to evaluate the sustainability of such a programme, its cost effectiveness, and the potential to scale it up to meet needs in other high neonatal mortality regions of Andhra Pradesh and elsewhere.

## Methods/Design

### Endpoints of the study

The primary outcome of the study is neonatal mortality. Secondary outcomes will include age at and cause of neonatal death, neonatal morbidity, maternal mortality and morbidity, health service usage, costs and several process and knowledge outcomes.

We will not be dividing foetal losses into miscarriages or stillbirths for two reasons: firstly, gestational age is not reliably reported; secondly, since women in the intervention arm may report pregnancies earlier than women in the control arm, we anticipate there could be a bias in the measurement of gestational age, and this bias may differ across the two arms of the trial.

### Type of study

The trial is a cluster-randomised controlled trial involving 464 villages, with the village as the primary unit of randomisation. This is an unblinded study as, following randomisation, participants and their caregivers will be aware of whether or not they are in an intervention village or control village. For outcomes such as death, this lack of blinding is unlikely to lead to outcome assessment bias.

### Randomisation

Villages will be stratified according to whether their travel time to the nearest designated NPHC is less or greater than one hour, and also into three groups according to whether the village is thanda (2–3 km from the main village with around 15 families), penta (20–30 km from the main village with around 4–5 families) or non-tribal (a main village). All villages will be randomly allocated, within each of these six strata, to either the intervention or control group.

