### Enrolment – Trial site(s) and participants

The trial site is the Nagarkurnool division of Mahabubnagar district in the Indian state of Andhra Pradesh. The trial will involve only those villages in the division with a population of less than 2,500 people. This criterion was decided upon in light of the fact that larger villages and towns generally have better access to health services, lower neonatal mortality rates, and therefore less potential to benefit from the interventions. Under this criterion, a total of 464 villages will be eligible for the trial with a total population of approximately 300,000 people.

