### Sample size calculation

The sample size has been calculated to give 80% statistical power to show a reduction in neonatal mortality that is statistically significant using a conventional 2-sided significance level of 5% if the true effect of the package of interventions is to reduce neonatal mortality by 25%. We assumed 4.38% neonatal mortality in the control villages (and hence 3.29% neonatal mortality in the intervention villages), an average population of 659 per village, a birth rate of 23 per 1000 population (giving rise to an average of 38 births per village over a period of 2.5 years) and an intra-cluster correlation coefficient of 0.00644 [20,6]. Under these assumptions we require 330 villages to detect a 25% reduction in neonatal mortality.

In the trial area, however, women who are expecting their first child usually move back to their mother's village around one to three months before the expected date of delivery. This migration could reduce the measured effect of intervention if women move from control villages to intervention villages and vice-versa. According to the NFHS-2, 36% of all births are first births in Andhra Pradesh. We assume that 90% of these women temporarily migrate and on the basis of this that 8% of control women actually deliver in an intervention village, whilst 24% of intervention women will deliver in non-intervention villages (8% in control group villages and 16% in villages outside of the study area) [20]. Assuming that both groups incur half the benefits of the intervention, the expected neonatal mortality rates in the two groups become 4.34% and 3.42%. Under this scenario 464 villages will still give 80% statistical power to show a reduction in neonatal mortality that is statistically significant at the 5% level.

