### Analysis strategies

The main analysis will assess the effect of the interventions on the primary and secondary outcomes. Primary analysis of the outcome(s) will follow the intention to treat principle (i.e. the participants will remain in the group they were randomised to and not analysed according to the interventions actually received), and will account for clustering.

For the primary outcome (neonatal mortality), the relative risk with a 95% confidence interval will be reported, taking appropriate account of clustering. A generalised linear model (without adjustment for covariates) using robust standard error estimates will be used to carry out this analysis. A further analysis will adjust for distance to nearest healthcare centres (public and private) and migration.

For secondary binary outcomes, including neonatal morbidity, maternal mortality and morbidity, and health service usage, relative risks will be estimated in an analogous fashion. For continuous outcomes t-tests with robust SEs will be carried out. ANCOVA (with robust standard errors) will be used where baseline adjustment is required. Bootstrapping will be used for non-normal outcomes and Cox models for survival analysis. A full analysis plan is given in the operations manual.

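### Village population is known in advance and linked to neonatal mortality, but is controlled only coarsely: adding it to the primary model would be a small, nearly free gain in precision

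*Protocol article*

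**What the plan says.** Three sections of the protocol article bear on this point.

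- **Enrolment – Trial site(s) and participants** restricts the trial to villages below 2,500 people because "larger villages and towns generally have better access to health services, lower neonatal mortality rates". Applying that limit requires a population figure for every candidate village.
- **Randomisation** names two stratifiers. On the first it says "Villages will be stratified according to whether their travel time to the nearest designated NPHC is less or greater than one hour". The second is settlement type: thanda (about 15 families), penta (4–5 families) or main village. This makes six strata, and all main villages on the same side of the one-hour line share one stratum.
- **Analysis strategies** fixes the primary analysis as "A generalised linear model (without adjustment for covariates) using robust standard error estimates". The one further analysis described adjusts for distance to health centres and for migration. Neither analysis lists population or settlement type.

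**The concern.** A baseline quantity that the protocol associates with the primary outcome, and that is already held for every cluster, is left out of the primary model. It is represented in the randomisation only through settlement type. Main villages can run up to 2,500 people, and their size is left to chance.

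Births scale with population, so the larger villages carry most weight in a relative risk computed over births. If mortality falls with size inside the eligible range, two things follow. A chance excess of large villages in one arm moves the estimate. The between-village variation that size explains also stays in the robust standard error. Because the model omits the strata as well, its standard error does not recover the precision that stratifying by settlement type and travel time may have bought.

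**Working it through.** **Reproducing the plan's figures.** From Sample size calculation: "The sample size has been calculated to give 80% statistical power" at two-sided 5%; "We assumed 4.38% neonatal mortality in the control villages", "hence 3.29% neonatal mortality in the intervention villages"; ICC 0.00644; 464 villages.

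- Births per village: 659 × 0.023 × 2.5 = 37.9, stated as 38.
- Design effect: 1 + (38 − 1) × 0.00644 = 1.238.
- Undiluted, two proportions with continuity correction: 5,054 births per arm; 5,054 × 1.238 / 38 = 164.7, so 165 per arm and 330 villages, as stated.
- Dilution by migration: the difference is 4.38 − 3.285 = 1.095. Control 4.38 − 0.08 × 0.5 × 1.095 = 4.34%; intervention 3.285 + 0.24 × 0.5 × 1.095 = 3.42%, as stated.
- Diluted: 466 villages with continuity correction, 452 without, against 464 stated. Power of 464 villages without correction is 81.1%.

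**Where the births are.** Assume five people per family (not in the documents). A thanda then has 15 × 5 = 75 people and a penta about 22. If 30% of the 464 were thandas and 5% pentas (assumed), they would hold (0.30 × 75 + 0.05 × 22) / 659 = 3.6% of the population, leaving about 96% in main villages. The Glossary gives a thanda around 100 households, that is 500 people on the same assumption. Thandas would then hold 0.30 × 500 / 659 = 23%. Main villages dominate either way, but the two descriptions of a thanda need reconciling.

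**Ceiling on the gain.** At equal village sizes the between-village part of the variance is 0.238 / 1.238 = 19%, so no village-level covariate can remove more than that. Removing all of it would raise power from 81.1% to 88.6%. If size explained 10, 25 or 50% of the between-village variance (assumed), power would be 81.9, 83.0 or 84.9%.

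**Gain under assumed gradients.** This was simulated with 464 villages, mean population 659, an assumed size distribution with CV about 0.93–0.96, arms balanced on settlement type, and 3,000 replicates per gradient. Between-village CV² of mortality was 0.00644 × (1 − 0.0438) / 0.0438 = 0.14.

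| Mortality ratio per doubling (assumed) | Cut in variance of log RR | Cut in squared robust SE |
|---|---|---|
| 0.95 | about 0% | about 0.5% |
| 0.90 | about 1% | about 2% |
| 0.85 | about 3% | about 4% |
| 0.80 | about 7% | about 8% |

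**On the plan's scale.** The diluted log relative risk is ln(3.42 / 4.34) = −0.238. Power of 81.1% means 0.238 / SE = 1.960 + 0.882 = 2.842, so SE = 0.084.

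- 3% cut: 2.842 / √0.97 = 2.886, power 82.3%; 0.03 × 464 = 14 villages.
- 7% cut: 2.842 / √0.93 = 2.947, power 83.8%; 0.07 × 464 = 32 villages.
- Implied SD of the shift from chance size imbalance: √0.03 × 0.084 = 1.5% and √0.07 × 0.084 = 2.2% on the relative risk, against a planned diluted value of 3.42 / 4.34 = 0.79.

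**The case against.** The case for leaving the plan alone is substantial, and most of it stands.

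- **Size is not absent from the design.** The 2,500 limit truncates it, and settlement type separates the smallest places from main villages. A reader might infer that size enters nowhere, or that it is the only mortality predictor the protocol names. Neither is right. The Background also points to higher rates in tribal and rural areas and to inaccessible care, and both are reflected in the strata.
- **No gradient below 2,500 is stated.** The sentence on larger places justifies excluding them. A gradient among the eligible villages is plausible, but every figure above that depends on one is conditional on an assumption.
- **Nothing is invalid.** A reader might infer a biased estimate or an unreliable test. Chance imbalance under randomisation is not bias. Robust standard errors carry the residual between-village variation, and the ICC allows for it in the sample size. That allowance does treat every village as having 38 births. With the design effect 1 + ((1 + CV²) × 38 − 1) × ICC and an assumed size CV of 0.5 or 1.0, power would be 79.2% or 73.8%. So there may be less slack than the plan suggests, but unequal village size is a separate matter from adjusting for it.
- **An unadjusted primary relative risk is a legitimate choice**, and the article refers to a full analysis plan in an operations manual that is not shown. That manual may hold further adjusted analyses. The article nevertheless fixes the primary model as having no covariates, so this is a stated choice and not an omitted detail.

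What survives is that size among main villages is uncontrolled, the data to control it are in hand, and the primary model uses neither size nor the strata.

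**Conclusion.** The point holds as a modest efficiency matter. Adjusting for log population would cut the variance of the log relative risk by roughly 0 to 7% for gradients of 0.95 to 0.80 per doubling, and by about 3% at 0.85. At the planned sample size that is at most about three points of power, from 81.1% to 83.8%. The steep end is demanding: 0.80 per doubling means mortality roughly halves over three doublings (0.80³ = 0.51), for example from 300 to 2,400 people.

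These figures rest on an assumed gradient, an assumed size distribution and an assumed mix of settlement types, because the protocol gives only a mean population. They do not show that the trial is underpowered on this account, or that the planned primary analysis would mislead. The reason to act is that the remedy uses data already held. Fixing it in advance also avoids a later dispute if the arms happen to differ in size.

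**What to change.** - In Analysis strategies, pre-specify log village population as a covariate in the primary generalised linear model. Use the figure applied for the 2,500 limit, frozen before randomisation.
- Preferably add the randomisation strata. Penta strata will contain few births, so enter travel time and settlement type as main effects (one and two terms), or set a rule in advance for merging sparse cells.
- Keep the unadjusted relative risk as a supporting result. With a log link and a constant effect across village sizes, both analyses estimate the same relative risk.
- If randomisation has not happened, also split the main-village strata into two or three population bands.

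The cost is about one degree of freedom out of 464 clusters for log population and a few more for the strata. Bands need a small change to the randomisation program. No new data, villages or staff are required. If size proves unrelated to mortality, adjusting for it gains no precision.

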The intervention team will train a total of approximately 250 VHWs (at least one for every village, in certain villages we may have to train more than one) and approximately 20 midwives (16 midwives delivering fixed day services in teams of two and 4 midwives based at NPHCs). They will go through a orientation program and training of not less than 10 days. This residential training will have both theoretical and practical components. It will be given by experts in the field of maternal and neonatal health care.

Additionally midwives will be trained to update a trial-specific health card provided to all eligible women in intervention villages. These cards will track the various services each woman in the intervention group has received under the programme, including immunizations, participation in health groups, regular checkups and hospitalisation. The VHWs and midwives will ensure that these cards are filled correctly and on time by the various health care providers. The midwives will also keep a record of the number of visits they have made to the village, the number of women they have met, the number of emergency deliveries with which they have assisted and the number of cases they have referred to the NPHCs. Midwives will also keep records of the nature of care they provide to each mother and child attended.

For reinforcement of messages, the VHWs and midwives will be given a manual to refer to for review. Regular meetings will be held to allow them to share knowledge regarding their work and problems encountered.

• Providing health education through a public information campaign

One of the most important contributors to poor maternal and neonatal health is a lack of good health information. This problem is particularly apparent in the local delivery and infant rearing practices which are often in contradiction of evidence-based good practice.

Health knowledge and awareness will be generated through frequent village meetings and community events. A health education campaign including theatre, films, focus groups and other media will be launched to promote key themes related to maternal and child health in each village. Folk culture in the form of song and dance will also be adapted to convey important messages to communities. All members of the community, not just women eligible for the trial, will be targeted by these campaigns.

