#### Contracting out primary and secondary health services to non-public institutions

As outlined in the trial justification, the supply of primary health care in the trial area is inadequate. Required improvements to the public sector were estimated to be prohibitively expensive, and evidence suggests the private sector may be able to provide primary care which is superior to that provided by the public, and potentially at a lower cost [11].

To increase supply of health services, the trial's intervention will designate up to 5 NPHCs to provide primary and secondary level care, made accessible through enhanced emergency transportation. NPHCs will be selected which are equipped with sufficient infrastructure and human resources. It is imperative to provide women in the intervention arm with quality services which are otherwise unavailable or inadequate, as it is expected that the educational component of the intervention will lead to greater awareness of the need for health services, and thus greater uptake of these services.

The list of candidate NPHCs will be drawn-up based on professional capability, existing infrastructure, and public perception of the facility (public perception serves as a way to introduce community participation in the selection process and to render the process transparent). Tie-ups with such facilities will initially be for the period of 3 months after which a favourable review would lead to a 6 month renewal of the contract. Any kind of primary or secondary service that an expectant mother would require during her pregnancy and for one month of the life of her baby would be covered by these facilities. By virtue of the contractual agreement, these NPHCs would be expected to provide around-the-clock service, admission to the general ward, food for the patient and one attendant, drugs, and disposables.

This contract will be subject to a per-patient cost ceiling. A rigorous monitoring system will buttress against over-billing and over-provision of services by the NPHCs.

Transportation will not be part of this contracting system, but will be provided directly at the village level for pick-up and drop off of patients at the NPHCs.

A detailed third party assessment of the quality of the services by the NPHCs will be conducted periodically by a committee of health and other professionals.

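### Stratifying by which NPHC serves a village, and adjusting for it, would recover a little precision that the plan gives away; the primary error bars are not invalidated

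*Protocol article*

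**What the plan says.** The unit of randomisation is the village: "The trial is a cluster-randomised controlled trial involving 464 villages, with the village as the primary unit of randomisation". Allocation is half and half: "The package of interventions will first be introduced in half of the villages with the others serving as controls".

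The Randomisation section defines two stratifiers. The first is a time band: "Villages will be stratified according to whether their travel time to the nearest designated NPHC is less or greater than one hour". The second is village type (thanda, penta or non-tribal). Together they give six cells: "All villages will be randomly allocated, within each of these six strata, to either the intervention or control group". Neither factor records which NPHC is the nearest one.

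Providers above village level are few. On the NPHCs: "the trial's intervention will designate up to 5 NPHCs to provide primary and secondary level care". On the midwives: "16 midwives delivering fixed day services in teams of two and 4 midwives based at NPHCs", which makes 8 mobile teams. The Community Health Promotion section also plans about 250 village health workers, at least one per village.

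The Sample size calculation uses a single correlation, "an intra-cluster correlation coefficient of 0.00644", applied to births within a village. The Analysis strategies section gives the primary model: "A generalised linear model (without adjustment for covariates) using robust standard error estimates will be used to carry out this analysis". A further analysis adjusts for distance to health centres and for migration, but not for which centre serves the village. The level of clustering is not named, and the full analysis plan is said to be in the operations manual.

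**The concern.** Under these rules, two villages at opposite ends of the division, looking to different NPHCs, can share a stratum. If mortality differs between catchments, two things follow. The arms can receive unequal shares of a high-mortality catchment by chance. The between-catchment part of the variance also stays in the standard error, because neither the design nor the primary model removes it. The information needed to avoid this is already in hand, since the travel-time stratum cannot be assigned without first identifying the nearest NPHC. After allocation, stratification cannot be added.

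A second, separate matter arises from the Objectives section, which includes scale-up to other regions. Intervention villages share at most 5 NPHCs and 8 midwife teams. If some providers do better than others, intervention villages with the same provider have correlated outcomes. The power calculation makes no allowance for that, and the article describes no comparison by catchment that would show whether the effect depends on a few providers.

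**Working it through.** **Inputs from the protocol article.** 464 villages, so 232 per arm; births per village 659 × 23/1000 × 2.5 = 37.9; ICC 0.00644; rates after allowing for migration 4.34% and 3.42%; two-sided 5% level.

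**Step 1: reproduce the stated sample size.** Design effect = 1 + (37.9 − 1) × 0.00644 = 1.238. The standard two-proportion formula with continuity correction, times 1.238, divided by 37.9 and doubled, gives 330 villages for 4.38% v 3.29% (stated: 330) and 466 for 4.34% v 3.42% (stated: 464). A village-level ICC alone is enough to reach the plan's figures, so no provider-level term is in them.

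**Step 2: power as planned.** Births per arm = 232 × 37.9 ≈ 8,791. SE of the difference = √[(0.0434 × 0.9566 + 0.0342 × 0.9658) × 1.238 / 8,791] = 0.00324. Power = Φ(0.0092/0.00324 − 1.96) ≈ 81%, without continuity correction.

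**Step 3: gain from stratifying and adjusting.** Suppose a share f of the village ICC lies between catchments and is removed. The design effect becomes 1 + 36.9 × 0.00644 × (1 − f). The article gives no value for f.

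| f (assumed) | Design effect | Power |
|---|---|---|
| 0 (as planned) | 1.238 | 81% |
| 10% | 1.214 | 82% |
| 25% | 1.178 | 83% |
| 50% | 1.119 | 85% |

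**Step 4: chance imbalance.** With 5 equal catchments (assumption), each has 464/5 ≈ 93 villages. If exactly half of the 464 are allocated without regard to catchment, the SD of the number going to intervention is √[93 × ¼ × (464 − 93)/463] = 4.3. A 2-SD split is about 55 v 38.

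**Step 5: are the error bars still valid?** In simulations (4,000 replicates, village-robust standard errors) with area differences common to both arms at CVs of 10% to 30% and no area stratification, type I error was 4.4% to 5.3% and power 81% to 82%. Area differences are then simply part of the between-village variance. With area stratification but an unadjusted model, type I error fell to 3.9% at a CV of 30%: the standard error is then too large, and the gain is lost unless the model includes the factor.

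**Step 6: provider correlation, for the scale-up inference only.** An ICC r among births sharing a provider, in the intervention arm only, adds 0.0342 × 0.9658 × r / J to the variance, with J = 8 teams or 5 NPHCs. No value of r is in the article; the range below is assumed.

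| r (assumed) | CV of provider mortality | Power, J = 8 | Power, J = 5 |
|---|---|---|---|
| 0.0001 | 5% | just under 80% | 79% |
| 0.00025 | 8% | 77% | 75% |
| 0.0005 | 12% | 74% | 70% |
| 0.001 | 17% | 67% | 60% |

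These use a normal critical value, which is optimistic with so few providers.

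**The case against.** The strongest reply is that nothing here is an error. Power is already above the 80% target, the trial is randomised at village level, and further stratification is a preference about precision. That is largely right, and it sets the weight of the point.

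A reader might infer more than the document supports, in four ways.

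- **That the few NPHCs and teams deliver the whole package.** They do not. Village health workers make home visits, give one-to-one education, assist home deliveries and organise discussion groups, and transport is arranged at village level. Much of the intervention varies at the level that the ICC already covers.
- **That the primary error bars are wrong.** Step 5 shows that missing area strata do no harm to validity. Provider correlation is a different matter, but it bears on generalising to other providers. If the package has no effect through any provider, that variation vanishes and the test of the primary outcome keeps its level. The clustering level is also left to the operations manual, although village is the natural reading.
- **That Table 2 proves area matters here.** Its spread of infant mortality, 62 to 140 per 1000, is between divisions; the trial lies wholly within one of them, Nagarkurnool.
- **That stratifying by NPHC would cure provider correlation.** It balances differences common to both arms. It cannot remove correlation that exists only in the intervention arm.

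The top of the range in Step 6 is also severe. A CV of 17% around 3.42% spans about 2.3% to 4.6%, so some providers would have no effect while others nearly halve mortality. Finally, NPHC contracts run for 3 months and then 6 on a favourable review, so the provider behind a catchment may change.

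**Conclusion.** The point holds as a modest loss of precision with a nearly free remedy that is available only before allocation. The gain is about 1 to 4 percentage points of power for between-catchment shares of 10% to 50%, together with protection against an uneven split of catchments. It depends on the assumed share and on the analysis adjusting for the factor.

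The sample size rests on village-level correlation only, which is confirmed by reproducing 330 and, within rounding of the inputs, 464. The margin above 80% is thin, but how much provider correlation would erode it for inference to other providers cannot be fixed from the article. That calls for a sensitivity analysis and a sentence on what the power covers. It does not show that the primary analysis is invalid.

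**What to change.** In Randomisation, add the nearest designated NPHC (up to 5 levels) as a stratification factor. Base it on the designation in force at allocation and keep it unchanged if contracts later change. This gives up to 30 cells averaging about 15 villages; merge sparse penta cells by a rule written down beforehand.

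In Analysis strategies, include NPHC catchment and the existing strata in the primary model, still with robust standard errors. Add a sensitivity analysis for the scale-up aim: the relative risk in each catchment with a random-effects summary.

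In Sample size calculation, state that the 80% power allows for correlation within villages only.

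The cost is one factor already known for every village, a few merged cells, a short analysis paragraph and one added sentence. The random-effects interval will be wider than the primary one and, with at most five catchments, imprecise.
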